### 5.2 Exclusion Criteria

- Acute promyelocytic leukemia (M3 AML) patients
- Patients with incomplete MRD data or key prognostic variables
- Secondary AML or therapy-related AML cases
- Patients with insufficient follow-up data

### 5.3 Sample Size Justification

The initial TARGET-AML cohort included 1,205 pediatric patients with non-M3 AML. Based on power calculations for detecting a hazard ratio of 2.0 for EFS with 80% power at α=0.05, the available sample size provides adequate statistical power for the proposed analyses. The cohort characteristics demonstrate balanced representation across key prognostic subgroups.

## 6. Methods

### 6.1 Data Collection Procedures

Data will be extracted from the TARGET database using standardized data collection forms. The following variable categories will be included:

- **Demographic data**: Age at diagnosis, gender, ethnicity
- **Disease characteristics**: WBC count at diagnosis, bone marrow and peripheral blast percentages, FAB classification, central nervous system involvement status
- **Genetic markers**: Karyotype, FLT3-ITD, NPM1, CEBPA, and WT1 mutation status
- **Treatment data**: Chemotherapy protocol, response assessment after each induction course, stem cell transplantation details
- **MRD data**: Quantitative MRD levels after Induction Courses 1 and 2
- **Outcome data**: Event-free survival, overall survival, relapse details

### 6.2 MRD Assessment Methodology

MRD was quantified using standardized multiparametric flow cytometry protocols with a minimum sensitivity of 0.01%. The methodology included:

- **Sample processing**: Bone marrow aspirates collected at the end of Induction Courses 1 and 2
- **Antibody panels**: Standardized 8-color flow cytometry panels targeting leukemia-associated immunophenotypes
- **Analysis protocol**: A minimum of 500,000 events were acquired using BD FACS Canto II flow cytometers
- **Quality control**: Regular instrument calibration and compensation controls using compensation beads
- **Data interpretation**: Expert hematopathologist review of all MRD assessments

### 6.3 Variable Definitions

- **Event-free survival (EFS)**: Time from diagnosis to first event (induction failure, relapse, secondary malignancy, or death from any cause)
- **MRD positivity**: Defined using two thresholds: traditional (≥0.1%) and novel (≥0.05%)
- **Complete remission**: <5% blasts in morphologically normal bone marrow with recovery of peripheral counts
- **Genetic risk groups**:
  - Low risk: inv(16)/t(16;16) or t(8;21)
  - High risk: monosomy 7 or del(5q)
  - Standard risk: All other cases with adequate cytogenetic data

### 6.4 Data Quality Assurance

- Double data entry for key variables with discrepancy resolution
- Range checks for continuous variables
- Consistency checks across related variables
- Missing data assessment and appropriate handling strategies

## 7. Statistical Analysis Plan

### 7.1 Primary Analysis

**Survival Analysis**: Kaplan-Meier method will be used to estimate EFS distributions stratified by MRD status at both thresholds. The log-rank test will compare survival curves.

**ROC Analysis**: Receiver operating characteristic curves will determine the optimal MRD threshold for predicting 5-year EFS status using Youden's index.

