## 3. Research Objectives and Hypotheses

### 3.1 Primary Objectives

1. To determine the optimal MRD threshold for predicting 5-year event-free survival following Induction Course 1 and Course 2 chemotherapy using ROC curve analysis.
2. To compare the prognostic discrimination capacity of the traditional 0.1% MRD threshold versus a proposed 0.05% threshold through Kaplan-Meier survival analysis and hazard ratio calculations.
3. To quantify the improvement in risk classification accuracy using net reclassification improvement (NRI) analysis when applying the lower MRD threshold.

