### 3.3 Research Hypotheses

- **Primary Hypothesis**: An MRD threshold of 0.05% provides superior prognostic discrimination compared to the conventional 0.1% threshold for predicting 5-year EFS in pediatric AML.
- **Secondary Hypothesis**: The 0.05% threshold demonstrates consistent prognostic performance across all genetic risk categories and offers significant net reclassification improvement.

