### 7.2 Secondary Analyses

**Cox Regression**: Univariate and multivariate Cox proportional hazards models will assess the association between MRD thresholds and EFS, adjusting for relevant covariates. **Net Reclassification Improvement**: Categorical NRI will quantify improvement in risk prediction using the novel threshold. **Subgroup Analysis**: Consistency of the MRD threshold will be evaluated within predefined genetic risk categories.

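### The primary analysis in 7.1 contains no inferential comparison of the 0.05% and 0.1% thresholds, although the primary hypothesis is that 0.05% discriminates better

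*Protocol*

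**What the plan says.** The primary hypothesis in Protocol 3.3 is that "An MRD threshold of 0.05% provides superior prognostic discrimination compared to the conventional 0.1% threshold for predicting 5-year EFS". Primary objective 2 in 3.1 is to "compare the prognostic discrimination capacity of the traditional 0.1% MRD threshold versus a proposed 0.05% threshold through Kaplan-Meier survival analysis and hazard ratio calculations".

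Section 7.1 lists two primary analyses:

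- **Survival curves.** "Kaplan-Meier method will be used to estimate EFS distributions stratified by MRD status at both thresholds. The log-rank test will compare survival curves".
- **ROC.** Youden's index is used to find the best MRD cut-point for 5-year EFS status. This serves primary objective 1, which names both induction courses.

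Section 7.2 lists the Cox models as secondary, together with NRI: "Categorical NRI will quantify improvement in risk prediction using the novel threshold". No interval or test is attached to the NRI.

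Section 6.3 defines MRD positivity as at least 0.1% or at least 0.05%, so the two classifications are nested. Section 5.3 bases adequacy of the sample on a hazard ratio of 2.0 with 80% power at α = 0.05 and 1,205 patients.

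**The concern.** The two classifications place every patient in the same class except those with MRD from 0.05% to below 0.1% (the band). The hypothesis therefore turns on whether moving the band from negative to positive sorts patients better by 5-year EFS. A log-rank test at one threshold asks something else: whether positive and negative patients differ at that cut. If MRD at or above 0.1% is strongly prognostic, the answer will be yes at both cuts, whatever the band does.

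The two hazard ratios have the same limit. Each describes one split, the splits share most of their patients, and no contrast between them is specified.

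At stake is the study's main question. As 7.1 stands, its tests can give the same result when the hypothesis is true and when it is false. The one listed method that directly contrasts the classifications has no settled status.

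**Working it through.** **1. What each method contrasts, and its status**

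| Method | Contrast | Called primary in | Called secondary in |
|---|---|---|---|
| Kaplan-Meier, log-rank | MRD+ v MRD-, per threshold | 1 (curves), 3.1, 7.1 | none |
| Hazard ratios, Cox | MRD+ v MRD-, per threshold | 1, 3.1 (objective 2) | 7.2; 4.5 (multivariate) |
| ROC, Youden | selects a cut-point over the whole range | 1, 3.1, 7.1 | none |
| Categorical NRI | 0.05% v 0.1% classification | 1, 3.1 (objective 3) | 3.3, 4.5, 7.2 |

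The only row that contrasts the two thresholds is the one that 7.1 leaves out.

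**2. The plan's power statement**

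Section 5.3 gives no required number of patients or events, so there is no figure to reproduce. With its inputs and a two-sided test (assumed), Schoenfeld's formula is D = (1.960 + 0.842)² / [p(1 − p)(ln 2)²], where p is the MRD-positive share.

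- p = 0.50: 7.849 / (0.25 × 0.4805) = 65.3, so 66 events.
- p = 0.25: 7.849 / (0.1875 × 0.4805) = 87.1, so 88 events.

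Section 2 puts 5-year EFS at about 50-60%. Taking 40-50% of patients with an event gives 482 to 603 events among 1,205. The claim of adequate power is right for MRD+ against MRD- at one threshold. It does not address the between-threshold comparison.

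**3. Can the log-rank tests separate the hypothesis from its opposite?**

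Assumptions: 1,205 patients, 25% at or above 0.1%, 5% in the band, and a hazard ratio of 2.0 for at least 0.1% against below 0.05%. There were 1,000 runs per row. The protocol gives neither share.

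| Band hazard ratio v <0.05% | Log-rank at 0.1% significant | Log-rank at 0.05% significant | 0.05% statistic the larger |
|---|---|---|---|
| 1.0 (0.1% is the right cut) | 100% | 100% | 1.8% |
| 1.5 | 100% | 100% | 53.1% |
| 2.0 (0.05% is the right cut) | 100% | 100% | 95.8% |

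Band shares of 3% and 10% also gave 100% in both significance columns. The relative size of the two statistics carries some information when the truth is clear-cut, but 7.1 states no rule that uses it.

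**4. What a direct contrast gives**

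For two binary classifications the two-category NRI is ΔSens + ΔSpec. That equals the difference in Youden's index and, since AUC = (Sens + Spec)/2 for a binary marker, twice the difference in AUC. With nested cuts it reduces to P(band | event) − P(band | no event).

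Take 5-year EFS of 62% below 0.05% (assumed) and a band hazard ratio of 1.5:

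- Event probabilities: 0.380 below 0.05%; 1 − 0.62^1.5 = 0.512 in the band; 1 − 0.62² = 0.616 at or above 0.1%.
- Overall: 0.70 × 0.380 + 0.05 × 0.512 + 0.25 × 0.616 = 0.445. Overall EFS is about 55%, inside the range in section 2.
- NRI = 0.0256/0.4455 − 0.0244/0.5545 = 0.0574 − 0.0440 = +0.0134.
- Standard error with complete 5-year status (537 events, 668 without): √(0.0574 × 0.9426/537 + 0.0440 × 0.9560/668) = 0.0128.
- 95% sampling range: about −1.2 to +3.9 percentage points.

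The same steps give −1.2 points for a band hazard ratio of 1.0 and +3.3 points for 2.0. The direct contrast changes sign with the truth, which the log-rank results do not, but it is imprecise. Section 5.1 requires only 36 months of follow-up for survivors, so censoring before 5 years will widen these ranges.

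**5. Power for the band against <0.05%**

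With 25% at or above 0.1%, 904 patients lie below 0.1%. A 5% band is 60 of them, so p = 0.05/0.75 = 0.067. With 40-50% events (assumed), power is 91-96% for a hazard ratio of 2.0 and 48-58% for 1.5. For 1.5 it is 24-28% with a 2% band and 74-84% with a 10% band.

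**The case against.** The strongest reply is that the plan does hold the head-to-head quantity. Youden's index at 0.05% minus Youden's index at 0.1% is the two-category NRI, ROC analysis is primary in 7.1, and NRI is primary objective 3. This stands in part. The raw material is there, and a reader who inferred that nothing in the plan bears on the comparison would go too far. But 7.1 uses Youden's index only to choose a cut-point, which may be neither 0.05% nor 0.1%. No contrast of the two and no interval is stated, and NRI is secondary in the analysis section.

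A second reply is that a separate statistical analysis plan may supply the detail. That would cover estimators and software. It would not cure objective 2 and 7.1 assigning within-threshold methods to a between-threshold hypothesis, nor the conflict over what is primary.

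Three stronger readings are tempting and are not supported:

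- **The plan's measures contradict each other.** With a band hazard ratio of 1.5, simulated hazard ratios were 1.95 at 0.1% and 1.91 at 0.05%, beside an NRI of +1.3 points. A gap of 0.04 set against an NRI whose sampling range includes zero does not show opposite directions.
- **Familywise error is inflated by a calculable amount.** The protocol does not fix a set of tests: Youden's index selects, and NRI only quantifies. The log-rank tests share patients, so a figure for independent tests has no basis.
- **A significant log-rank test will be presented as proof for 0.05%.** The protocol does not say how results will be weighed or reported.

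**Conclusion.** The concern holds in this form: 7.1 specifies no inferential comparison of 0.05% with 0.1%, and the one listed method that directly contrasts them is primary in two places and secondary in three. Hazard ratios carry the same conflict between 3.1 and 7.2.

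The mismatch follows from the text alone. Its size rests on assumed MRD shares, event rates and hazard ratios. Under those, both log-rank tests reach significance in every simulated run whether or not the band has a worse prognosis. The result does not show that 0.05% is the wrong threshold, or that the study is too small to compare the two; the band's size is unknown from the protocol. It does show that the power statement in 5.3 answers a different question. The point should be settled before the analysis starts.

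**What to change.** - **7.1:** make the primary test one paired comparison of the two classifications in the same patients for 5-year EFS, with a bootstrap 95% confidence interval and a method that allows for censoring before 5 years. The two-category NRI or the difference in 5-year time-dependent AUC will serve; they are the same contrast up to a factor of 2.
- **Time point:** name one induction course for this test and make the other secondary.
- **Support:** report EFS for the 0.05% to <0.1% group against <0.05% and against ≥0.1%. Treat the per-threshold Kaplan-Meier and log-rank results as descriptive.
- **Consistency:** align sections 1, 3.1, 3.3, 4.5, 7.1 and 7.2 on whether NRI and hazard ratios are primary or secondary.
- **5.3:** state that the power for a hazard ratio of 2.0 refers to MRD+ against MRD- at one threshold, not to the between-threshold comparison.

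The cost is wording and a little programming, with no new data. The price is a less precise primary result that may be less favourable to 0.05%.

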## 2. Research Background and Scientific Rationale

Pediatric acute myeloid leukemia represents a heterogeneous group of hematologic malignancies characterized by clonal proliferation of myeloid precursors with impaired differentiation. Despite significant advancements in risk-adapted therapy approaches, including allogeneic hematopoietic stem cell transplantation for high-risk patients, relapse remains the predominant cause of treatment failure, with 5-year event-free survival rates plateauing at approximately 50-60% in contemporary clinical trials. Minimal residual disease monitoring has emerged as a critical component of modern risk stratification in acute leukemias. Among various MRD detection methodologies, multiparametric flow cytometry-based MRD assessment offers the advantage of rapid turnaround time, widespread availability, and applicability to nearly all patients regardless of genetic markers. The conventionally accepted threshold of 0.1% for defining MRD positivity has demonstrated prognostic utility across multiple studies, yet evolving technological capabilities in flow cytometry warrant reevaluation of this standard. Recent evidence suggests that lower levels of residual disease, previously classified as MRD-negative by the 0.1% threshold, may still harbor significant prognostic implications. Technological advancements now enable reliable detection of leukemic cells at levels as low as 0.01%, raising important questions about the optimal threshold for clinical decision-making. This study addresses a critical evidence gap by systematically evaluating a lower MRD threshold in a large, well-annotated pediatric AML cohort.

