## 5. Study Population

### 5.1 Inclusion Criteria

- Pediatric patients (<18 years at diagnosis) with newly diagnosed de novo AML (non-M3 subtype)
- Availability of MFC-MRD data measured after completion of Induction Course 1 and/or Course 2
- Treatment according to one of the specified protocols: AAML03P1, AAML0531, or AAML1031
- Complete baseline clinical and molecular characterization data
- Minimum follow-up duration of 36 months for surviving patients

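### The Youden cut-off and the NRI are computed without regard to marrow blast count, so patients with overt leukaemia can bias the 0.05% versus 0.1% comparison toward the higher threshold

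*Protocol*

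**What the plan says.** Section 7.1 of the protocol sets the cut-off rule: "Receiver operating characteristic curves will determine the optimal MRD threshold for predicting 5-year EFS status using Youden's index". Entry to that analysis follows from eligibility. Section 5.1 asks for "Availability of MFC-MRD data measured after completion of Induction Course 1 and/or Course 2", and the nearest exclusion in 5.2 is "Patients with incomplete MRD data or key prognostic variables". Neither section has a blast-count or remission criterion, and the schema in 4.5 goes from eligibility and data extraction directly to stratification by MRD threshold.

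The protocol does hold what a restriction would need. Section 6.3 defines complete remission as "<5% blasts in morphologically normal bone marrow with recovery of peripheral counts", and 6.1 collects "response assessment after each induction course". Response information presumably feeds the outcome, since EFS in 6.3 is "Time from diagnosis to first event (induction failure, relapse, secondary malignancy, or death from any cause", in which induction failure and relapse both count. It defines no analysis set.

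The NRI in 7.2, which serves primary objective 3 in 3.1, carries no restriction either. Section 7.3 lists a landmark analysis at 3 months post-induction, as a sensitivity analysis and not linked to the ROC cut-off.

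**The concern.** Section 2 motivates the study by asking whether residual disease below the usual 0.1% limit still carries prognostic meaning. A patient whose marrow still holds, say, 30% blasts after Course 1 is positive at both thresholds and cannot inform that question. Such patients still affect the answer, because Youden's index and the NRI are scaled by all events and all non-events in the cohort. Since induction failure is itself an EFS event, some of these patients will be events almost by definition.

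The selected threshold then depends partly on how many patients were not in remission, and not only on what low-level MRD means. Primary objectives 1 and 3 in section 3.1 are both exposed.

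**Working it through.** The protocol states no cut-off estimate, MRD distribution or overt-disease share, so there is no plan figure to reproduce. The sample-size statement in 5.3 does not bear on this point.

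**Inputs from the protocol.** Thresholds 0.05% and 0.1% (6.3); cohort 1,205 (5.3); "5-year event-free survival rates plateauing at approximately 50-60% in contemporary clinical trials" (section 2), hence about 40-50% events.

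**Inputs assumed.** The overt-disease share, the event rate among those patients, and the slope of risk on MRD. Patients with 5% blasts or more are also taken to lie above 0.1% by flow. The 5% limit is morphological, so this is an approximation.

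**Step 1, direction.** Let the 0.05% to <0.1% window hold *a* events and *b* non-events, and the cohort *E* events and *N* non-events. Lowering the cut-off changes Youden's index by

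gain = a/E − b/N,

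which is positive only if a/(a+b) > E/(E+N). The window event rate must beat the cohort event rate. For two nested cut-offs all reclassification is upward, so the two-category NRI is the same expression. Overt-disease patients leave *a* and *b* unchanged. If their event rate exceeds that of the others, E/(E+N) rises and the bar rises with it.

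**Step 2, a count (assumed).** 1,000 patients with <5% blasts, 450 events, 40 patients in the window. Add 150 overt-disease patients with 80% events (120 events, 30 non-events), giving E = 570 and N = 580.

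| Window events | Without overt disease | With overt disease |
|---|---|---|
| 26/40 | 26/450 − 14/550 = +0.032 | 26/570 − 14/580 = +0.021 |
| 20/40 | 20/450 − 20/550 = +0.008 | 20/570 − 20/580 = +0.001 |
| 19/40 | 19/450 − 21/550 = +0.004 | 19/570 − 21/580 = −0.003 |
| 18/40 | 18/450 − 22/550 = 0.000 | 18/570 − 22/580 = −0.006 |

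The break-even window rate moves from 450/1,000 = 45% to 570/1,150 = 49.6%. With 60% events in the overt group it moves only to 540/1,150 = 47.0%, and 19/40 stays just positive (19/540 − 21/610 = +0.0008).

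**Step 3, the optimum.** Youden's index peaks where the event probability at that MRD value equals the cohort event rate π. Suppose risk is logistic in log10 MRD with odds ratio OR per tenfold rise. Raising π to π′ then moves the optimum from c to c′:

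log10(c′/c) = [logit π′ − logit π] / ln(OR).

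Start at c = 0.055% with π = 0.446, and add overt-disease patients equal to a fraction s of the others, with event rate e, so that π′ = (0.446 + s·e)/(1 + s). For s = 10%, e = 80%, OR = 2: π′ = 0.526/1.10 = 0.478; the logit difference is −0.087 − (−0.217) = 0.130; 0.130/0.693 = 0.187; c′ = 0.055 × 10^0.187 = 0.085%.

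| OR per tenfold | e | s = 5% | s = 10% | s = 15% |
|---|---|---|---|---|
| 1.57 | 80% | 0.078% | 0.107% | 0.142% |
| 2 | 80% | 0.069% | 0.085% | 0.102% |
| 3 | 80% | 0.063% | 0.072% | 0.081% |
| 1.57 | 60% | 0.064% | 0.073% | 0.083% |
| 2 | 60% | 0.061% | 0.066% | 0.072% |
| 3 | 60% | 0.059% | 0.062% | 0.065% |

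Three of the 18 cells reach 0.1%, all with e = 80%: OR 1.57 at s = 10% and 15%, and OR 2 at s = 15%.

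**Step 4, sampling error.** The standard error of a 45% rate in 40 patients is √(0.45 × 0.55/40) = 7.9 points, against a break-even shift of 4.6 points in step 2. In simulated cohorts of 1,205 with 45% events, a true optimum of 0.05% and no overt disease, the estimated optimum had a 5-95% range of about 0.02-0.12%. That range already spans both candidates.

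**The case against.** **The size is assumed.** This stands in full. A reader might infer that including overt disease is enough to push the optimum to 0.1% or above. The documents do not support that, because they give none of the three quantities that decide it, and most of the grid in step 3 stays below 0.1%. The sign change in step 2 is one patient wide and smaller than sampling error.

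**The bias runs against the primary hypothesis.** Section 3.3 expects 0.05% to be superior, so a finding in its favour would be conservative on this account. That also stands and lowers the severity. It does not help if the result favours 0.1% or is equivocal, since case mix and biology could not then be told apart.

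**All assessed patients are a legitimate target.** Objective 1 in 3.1 does not mention remission, and Youden's optimum depends on case mix in any population. This is a reason to keep the all-patient result in the report. It does not answer the question in section 2, which concerns patients now called negative.

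**Response data are used.** A reader might infer that the protocol collects response and then ignores it. That goes too far: induction failure and relapse presuppose response assessment and enter EFS. What is missing is an analysis set based on it.

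**The landmark analysis in 7.3 is a partial safeguard.** It would remove patients whose event had occurred by then. It is not tied to the ROC, and it could keep patients with overt disease after Course 1 who remitted after Course 2.

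**A separate analysis plan may define the set.** Section 7 bears the title of the statistical analysis plan and fixes none. If another document does, a cross-reference would settle the point.

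**Conclusion.** The point holds as a case-mix bias of known direction and unknown size. The ROC/Youden and NRI comparison includes patients with 5% blasts or more. If their event rate exceeds that of the other patients, the comparison shifts toward the higher threshold with no change in outcome among those at 0.05% to <0.1%. That condition is plausible, given that induction failure is an EFS event, but the protocol has no figure to confirm it. The shift shrinks if many patients with overt disease after Course 1 stay event-free, and it may differ between courses.

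Under the assumed ranges in step 3, an optimum near 0.055% moves to between about 0.06% and 0.14%. Youden's optimum is imprecise at this sample size in any case. This should be fixed because the repair is cheap and touches the central comparison. It does not invalidate the plan.

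**What to change.** In 7.1 and 7.2, for Course 1 and Course 2 separately:

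- Run the ROC/Youden analysis and the NRI comparison of 0.05% with 0.1% in patients with <5% morphologic blasts in the marrow from which MRD was measured. This is the blast part of the 6.3 remission definition, without count recovery, and the text should say so.
- Show patients with 5% blasts or more as a separate group.
- Report the all-patient result alongside.
- Give a bootstrap confidence interval for the selected cut-off.

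The cost is a few lines of protocol text and one filter based on the response data that 6.1 already collects. The primary set becomes somewhat smaller, and a hazard ratio for MRD-positive versus MRD-negative reported in it will be less extreme than in all patients. The set should be fixed before results are seen.

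### Primary objective 1 takes one Youden maximum as the optimal MRD threshold, with no stated precision, and the section 5.3 power statement is stretched to cover it

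*Protocol*

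**What the plan says.** The first primary objective in Protocol section 3.1 is "To determine the optimal MRD threshold for predicting 5-year event-free survival following Induction Course 1 and Course 2 chemotherapy using ROC curve analysis". Section 7.1 fixes the method: "Receiver operating characteristic curves will determine the optimal MRD threshold for predicting 5-year EFS status using Youden's index". It gives no interval for the cut-off and does not say how an estimate near both candidate values should be read. Section 6.3 names those candidates, 0.1% and 0.05%.

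Section 5.3 opens with "The initial TARGET-AML cohort included 1,205 pediatric patients with non-M3 AML". It continues "Based on power calculations for detecting a hazard ratio of 2.0 for EFS with 80% power at α=0.05" and concludes that "the available sample size provides adequate statistical power for the proposed analyses".

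The two fixed thresholds are also compared directly. The second primary objective is "To compare the prognostic discrimination capacity of the traditional 0.1% MRD threshold versus a proposed 0.05% threshold through Kaplan-Meier survival analysis" and hazard ratios, and the third uses net reclassification improvement.

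**The concern.** The candidates differ by a factor of two, which is 0.30 on the log10 scale. Near its maximum the Youden index is usually flat, so the cut-off that happens to maximise it in one sample can move a long way by chance. Section 7.1 nevertheless lets that single value settle what is optimal, separately after Course 1 and Course 2, and the two courses could return different values through sampling error alone.

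The sample-size text does not help. Power to detect a hazard ratio between two groups and precision in locating a cut-off are different properties, and section 5.3 calculates only the first. At stake is whether the report may call 0.05%, or any other value, the optimum. The Study Summary wants the results to support recommendations on MRD monitoring standards.

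**Working it through.** **1. The power statement.** Inputs from section 5.3 are HR 2.0, 80% power and α = 0.05 (taken as two-sided; the text does not say). The groups are taken to be MRD-positive and MRD-negative. The Schoenfeld formula gives events = (1.960 + 0.842)² / [(ln 2)² p(1−p)], with p the MRD-positive share:

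- p = 50%: 7.849 / (0.4805 × 0.25) = 65.3, so 66 events (Freedman: 7.849 × 9 = 70.6, so 71)
- p = 25%: 7.849 / (0.4805 × 0.1875) = 87.1, so 88
- p = 10%: 7.849 / (0.4805 × 0.09) = 181.5, so 182

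Section 2 puts EFS at "5-year event-free survival rates plateauing at approximately 50-60% in contemporary clinical trials". If that holds here, 40-50% of 1,205 patients is about 482-603 events. In the least favourable case (482 events, p = 10%) power is Φ(0.693 × √(482 × 0.09) − 1.96) = Φ(2.60), above 99%. The sample is adequate for this comparison. Nothing in the calculation concerns a cut-off.

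**2. The cut-off, smooth risk (binormal).** The MRD distribution, AUC and risk shape are assumptions; the protocol gives none of them. Log10 MRD is normal in patients with and without an event, with common SD and the true optimum at 0.05%. Values are censored at the 0.01% sensitivity in section 6.2; N = 1,205, the event share is 45% and 5-year status is known for all. The empirical Youden maximum was taken in 1,500 simulated samples per setting. The log midpoint is √(0.05 × 0.1) = 0.071%.

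| AUC | SD (log10) | Past midpoint | 95% sampling range | True difference in J | SE of difference |
|---|---|---|---|---|---|
| 0.60 | 1.0 | 31% | 0.014-0.196% | 0.0062 | 0.0186 |
| 0.65 | 1.0 | 26% | 0.018-0.144% | 0.0093 | 0.0184 |
| 0.70 | 1.0 | 25% | 0.022-0.123% | 0.0122 | 0.0182 |
| 0.60 | 1.5 | 40% | 0.011-0.359% | 0.0028 | 0.0156 |
| 0.65 | 1.5 | 33% | 0.011-0.252% | 0.0042 | 0.0154 |
| 0.70 | 1.5 | 30% | 0.014-0.181% | 0.0055 | 0.0152 |

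All six ranges contain both 0.05% and 0.1%. The last two columns show why. For AUC 0.65 and SD 1.0, the group means are √2 × 0.385 = 0.545 apart. The share of events between the two cut-offs is Φ(0.029) − Φ(−0.272) = 0.119, and of non-events Φ(0.573) − Φ(0.272) = 0.109, so J differs by 0.009. The SE is √(0.119 × 0.881/542 + 0.109 × 0.891/663) = 0.018, twice the difference.

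With the optimum at 0.1% as well, event shares of 40-50%, and with or without censoring, these AUC and SD values give about 20-40%.

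**3. The cut-off, smooth risk (logistic).** Here 40% of patients are undetectable and the rest log-uniform from 0.01% to 50%; the log-odds slope is 0.3 to 0.8 per tenfold. The cut-off is past the midpoint in 27-37% of samples if the optimum is 0.1% and 28-38% if it is 0.05%. For an optimum of 0.1% the 95% range runs from 0.033-0.31% (steep) to 0.015-0.76% (shallow). Only 0.6 × 0.301/3.699 = 4.9% of patients lie between the two thresholds, and J differs by 0.002-0.006.

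**4. More favourable and mixed cases.** With the binormal model and SD 0.7, the figure is 9-12% at AUC 0.75 and 7-9% at AUC 0.80. If risk steps up exactly at the true cut-off, it is 0-2% for a truth of 0.05% and 0.2-48% for a truth of 0.1%. In the widest-spread step settings the estimate drifts downwards, so the criterion counts the error only when the truth is 0.1%.

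**5. Sample size.** With 600-900 patients the six settings of step 2 give 25-42%. For AUC 0.60 and SD 1.0, 20,000 patients instead of 1,205 (16.6 times as many) narrow the 95% range from log10(0.196/0.014) = 1.15 to log10(0.086/0.029) = 0.47. That factor of 2.4 is near the cube root of 16.6 (2.55) and well short of the square root (4.07). A large cohort therefore buys less precision for a cut-off than for a hazard ratio.

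**The case against.** The strongest reply is that no input in the protocol fixes the error rate. That stands. A reader might infer that the rule cannot separate the two thresholds, or picks the wrong one in about one sample in three. The documents do not support either statement, because the result depends on an MRD distribution, AUC and risk shape that they do not give, and under sharper markers or some step patterns the error is small.

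Second, the split at 0.071% is a device of this check. The protocol returns a continuous cut-off and nowhere assigns it to the nearer candidate. Nor does the primary hypothesis, superior discrimination of 0.05% over 0.1%, depend on where the Youden maximum falls: Kaplan-Meier curves, hazard ratios and reclassification address it. This also stands and confines the point to objective 1.

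Third, in the moderate smooth-risk settings the cut-off wanders because the two values perform almost alike, so choosing the other one costs little. This too stands, and it changes the harm: what lacks support is the claim to have found the optimum.

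Fourth, section 5.3 might be read as underpowered, or the Youden rule faulted for lacking a 5% error rate. Neither follows. Power for HR 2.0 is ample, and a test's error rate is not the standard for an estimator. The fault is the extension to every proposed analysis.

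Finally, an interval for the cut-off may be in a separate analysis plan that is not shown. Its absence alone would not be a finding. What the protocol does fix is a point estimate that determines the answer and an adequacy claim that does not cover it.

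**Conclusion.** The point holds in a limited, conditional form. Objective 1 lets a single Youden maximum name the optimum, and section 5.3 claims adequacy that its hazard-ratio calculation cannot supply. At N = 1,205, with smooth risk, AUC about 0.60-0.70 and SD 1.0-1.5 log10, the estimate falls on the wrong side of the midpoint in about 20-40% of samples, and its 95% range usually contains both candidates. Other plausible assumptions give about 7-12% (sharper markers) or 0-48% (step in risk). The difference of about 0.002-0.012 in true Youden index applies to the moderate smooth-risk settings only.

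These figures are a best case for N and follow-up. Section 4.5 applies the eligibility criteria after the count of 1,205, and section 5.1 requires only 36 months of follow-up in survivors, so 5-year status may be unknown for some. The point should be corrected because it decides what objective 1 may conclude; it does not undermine objectives 2 and 3.

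**What to change.** In section 7.1, replace the sentence that lets the ROC curve determine the threshold with text to this effect:

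- For each induction course, the Youden cut-off will be reported with a bootstrap 95% interval on the log10 scale, resampling patients and repeating the whole selection. The index will be plotted against the cut-off.
- The ROC analysis favours 0.05% over 0.1% only if the interval contains 0.05% and lies wholly below 0.1%.
- It favours 0.1% over 0.05% only if the interval contains 0.1% and lies wholly above 0.05%.
- If the interval contains both values, the two are not distinguished.
- If it contains neither, neither is supported as the optimum.

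The interval should be described as approximate, because the maximiser of an empirical step function converges slowly and the ordinary bootstrap is not exact for it.

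In section 5.3, limit the power statement to the EFS hazard ratio between MRD-positive and MRD-negative patients, and say that it does not cover the location of the cut-off.

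The cost is a few sentences and a short bootstrap in R, with no new data. The downside is that the ROC result may often be reported as inconclusive between the two values.
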